### Sample size considerations

DB incidence after EMR in the right colon has been reported to range between 7 and 12.7% after EMR [6, 7]. Based on these studies, we believe that PC after standard EMR may be able to reduce delayed bleedings by 7.8% (from 9.8 to 2%) in a superiority design. With a 2-sided significance level of 5% (0.1% used as symmetric stopping boundaries during the interim-analysis, and 4.9% used as nominal significance level) and power of 80%, a total of 310 patients are required. With an estimated drop out of 15%, a total of 356 patients (2 × 178) are required to demonstrate this effect.

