### Assignment of interventions

#### Randomization and treatment allocation

Randomization will take place in a 1:1 ratio after complete radical EMR without a clinically indicated intraprocedural clip placement, using a web-based randomization module (Castor EDC, Amsterdam, The Netherlands). Participants are stratified by center with random block sizes of 2, 4, and 6 per stratum. A time schedule for the trial can be found in Table 1.

**Table 1 Tab1:** Schedule of enrolment, interventions, and assessments

	Study period						
	Enrolment	Allocation	Post-allocation				Close-out
Timepoint	Week − 1	EMR + 0	EMR+ 0	+ 1 month	+ 3 months	+ 6 months	+ 6 months

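### The 356 patients cover a drop-out of 12.9%, not the stated 15%: the allowance was computed as 310 × 1.15 instead of 310 / 0.85

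*Protocol article*

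**What the plan says.** All the figures stand in one paragraph of the protocol article, Sample size considerations.

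- Effect assumed: clipping will "reduce delayed bleedings by 7.8% (from 9.8 to 2%) in a superiority design".
- Error rate: two-sided 5% overall, with "0.1% used as symmetric stopping boundaries during the interim-analysis, and 4.9% used as nominal significance level".
- Size before drop-out: "power of 80%, a total of 310 patients are required".
- Size after drop-out: "With an estimated drop out of 15%, a total of 356 patients", given as 2 × 178.

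Under Randomization and treatment allocation: "Randomization will take place in a 1:1 ratio". The section on study withdrawal says that patients who withdraw are not replaced. The total of 356 recurs in the abstract and under Trial design, and the interim analysis is set at half of it (178).

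The article names no test or formula for the 310.

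**The concern.** A drop-out allowance has one purpose: once the expected share of patients is lost, the required number should remain. Here it does not. Anyone who later asks whether the observed loss was within plan would compare it with 15%, whereas the 310 is already lost once drop-out passes 12.9%. A loss between those two values would look provided for and yet leave fewer patients than the protocol says it needs. Because withdrawals are not replaced, the allowance is the only stated buffer after randomisation.

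**Working it through.** **Inputs** (Sample size considerations, except allocation): control rate p1 = 0.098; clip rate p2 = 0.02; two-sided nominal level 0.049; power 80%; 310 before and 356 after the allowance; drop-out 15%; allocation 1:1 (Randomization and treatment allocation).

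**Step 1: reproduce the 310.** The article names no test, so several were tried at the 0.049 level, always with equal arms.

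| Method | Total for 80% power |
|---|---|
| Fisher's exact test, power by full enumeration | 310 |
| Normal approximation, pooled variance | 286 |
| Normal approximation, unpooled variance | 282 |
| Pooled, with continuity correction | 336 |
| Arcsine | 254 |

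For Fisher's test, power is 79.85% at 154 per arm and 80.2% at 155 per arm, so 155 is the smallest equal-arm size that reaches 80%. Of the methods tried, only this one gives 310. That Fisher's test was used is an inference from this match, since the article does not say so.

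The pooled formula, for comparison, with mean rate (0.098 + 0.02)/2 = 0.059:

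n per arm = [1.9686 × √(2 × 0.059 × 0.941) + 0.8416 × √(0.098 × 0.902 + 0.02 × 0.98)]² / 0.078² = 142.9, so 143 per arm and 286 in total.

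**Step 2: reproduce the 356.** 310 × 1.15 = 356.5, which matches 356 (2 × 178). Dividing instead gives 310 / 0.85 = 364.7, which does not.

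**Step 3: check 356 against its purpose.**

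- Left after 15% loss: 356 × 0.85 = 302.6.
- Shortfall: 310 − 302.6 = 7.4 patients.
- Largest loss that still leaves 310: 1 − 310/356 = 46/356 = 12.9%.
- Enrolment needed at 15%: 365, or 366 as 2 × 183, which is 9 or 10 more than 356 (2.5% to 2.8%).

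None of these results depends on the choice of test.

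**Step 4: power with about 303 patients, two-sided 0.049.**

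| Patients left (control/clip) | Fisher's exact test |
|---|---|
| 151/151 | 78.8% |
| 152/151 | 79.4% |
| 151/152 | 84.5% |
| 152/152 | 79.2% |
| 155/155 (the stated 310) | 80.2% |

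The pooled normal approximation gives 82.3% at 303.

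In equal arms, Fisher's test loses 1.0 to 1.4 points against the 80.2% at 310. Moving one patient between arms at a total of 303 changes its power by about 5 points (79.4% against 84.5%). That swing comes from the discreteness of the exact test and is larger than the loss itself.

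**The case against.** The best defence accepts the arithmetic and disputes its importance.

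- **Power.** A reader might infer that the trial falls below its 80% power, or that 310 leaves no margin at all. The document does not support either. Both rest on Fisher's test, which the sample size section does not name, and on exactly equal arms. The planned primary analysis is a mixed-model regression that yields a relative risk, so the Fisher figures are not the power of that analysis either. Under the pooled normal approximation 286 patients suffice, and 303 give about 82%. This part of the defence stands in full.
- **Looser inputs.** The same paragraph cites reported bleeding rates from 7% to 12.7%, and the 15% is itself an estimate. Seven patients are small beside that uncertainty. This stands, and it limits the severity. It does not make the sentence correct.
- **What the 15% refers to.** Randomisation follows a completed resection, the primary outcome is read at 30 days, follow-up runs to a colonoscopy at 6 months, and the analysis is by intention to treat with imputation possible. Loss for the primary endpoint could therefore be well below 15%. The article does not say which time point is meant, so this is plausible but unproven. The paragraph itself applies the 15% to the number needed for the primary effect.

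Nothing in the defence makes 356 × 0.85 equal 310, and no other section repairs it.

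**Conclusion.** The sentence is wrong as written, with minor severity. With the article's own figures, 356 enrolled and 15% lost leaves about 303, some 7 below the stated 310; the true tolerance is 12.9%. This rests only on the three stated numbers and on reading drop-out as the share of enrolled patients who are lost, which is its usual meaning.

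The effect on power is small. It is about 1 point below 80% under Fisher's exact test in equal arms (78.8% at 2 × 151, 79.2% at 2 × 152), and power stays above 80% under the pooled normal approximation. Whether 80% is missed cannot be said without naming the test, so that claim should not be made.

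**What to change.** Replace the drop-out sentence with something like: *With 356 patients (2 × 178), the required 310 remain if drop-out is at most 12.9%; at 15% drop-out about 303 remain.* Then name the test used for the sample size and give its power at about 303. If that was Fisher's exact test, state the arm sizes with the figure (78.8% at 2 × 151, 79.2% at 2 × 152), because the result shifts with a one-patient imbalance.

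The cost is one or two sentences and a slightly less favourable stated allowance. The total of 356, the interim look at 178, the analysis and the error rates all stay as they are. Enrolling 366 (2 × 183) would make the 15% statement true, but it is optional and not needed to correct the text.

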### Study withdrawal

Subjects can leave the study at any time for any reason without any consequences. The investigator can decide to withdraw a subject from the study for urgent medical reasons. There will be no replacement of individual subjects after withdrawal.

### Assignment of interventions

#### Randomization and treatment allocation

Randomization will take place in a 1:1 ratio after complete radical EMR without a clinically indicated intraprocedural clip placement, using a web-based randomization module (Castor EDC, Amsterdam, The Netherlands). Participants are stratified by center with random block sizes of 2, 4, and 6 per stratum. A time schedule for the trial can be found in Table 1.

**Table 1 Tab1:** Schedule of enrolment, interventions, and assessments

	Study period						
	Enrolment	Allocation	Post-allocation				Close-out
Timepoint	Week − 1	EMR + 0	EMR+ 0	+ 1 month	+ 3 months	+ 6 months	+ 6 months
**Enrolment:**							
**Eligibility screen**	X						
**Informed consent**	X						
**Allocation**		X					
**Interventions:**							
***PC post EMR***			X				
***Questionnaires (EQ-5D*****,** ***iMCQ*****,** ***iPCQ)***			X	X	X	X	
***Control group without PC***			X				
**Assessments:**							
***Collect baseline and procedure variables***	X	X	X				
***Collect primary outcome variables***			X	X			
***Standard of care surveillance colonoscopy***						X	
***Collect secondary outcome variables***						X	X

#### Blinding

Patients will be blinded for treatment allocation whenever possible. However, patients undergoing EMR under conscious sedation cannot be blinded for treatment allocation. Whereas treating physicians cannot be blinded, the Outcome Adjudication Committee (OAC) evaluating the endpoints will be blinded for treatment allocation.

### Data collection and management

Coded study data will be collected in a web-based case record form (CRF) in Castor EDC. Patients will have the option to fill out the questionnaires with the end-to-end encrypted mobile “Improve” app (Open HealthHub, Utrecht, The Netherlands). After the data collection is complete, data are locked and saved for 15 years according to national law and regulations.

Missing data within a complete follow-up term will be prevented as much as possible. The reason for missing data will be reported. In case of > 5% non-selective missing data, multiple imputation may be performed. Sensitivity analyses will be performed with a different assumption for the distribution of the missing data than that was used in the primary analysis [24, 25].

### Statistical analysis methods

#### Primary analysis

Comparison of the primary endpoint DB will be performed according to intention-to-treat, using a mixed model regression analysis to correct for clustering of data, resulting in an estimated relative risk and 95% confidence intervals. Scale variables will be presented as mean ± standard deviation and in case of skewed distributions as median and range. Values will be compared by Student’s *T* test, Wilcoxon rank sum test, *χ*^2^ test, or Fisher exact test as appropriate. A two-tailed *p* value < 0.05 is considered statistically significant. A type 1 error will be controlled for by only taking one presentation of the primary endpoint (DB) per patient in the statistical analysis. In case of multiple presentations for bleeding, the highest gradation for severity will be included in the analysis. The outcomes of the intention-to-treat analysis will be compared to an exploratory per-protocol analysis.

In case of disbalances in baseline characteristics, potential confounders for DB will be determined with a *χ*^2^ test or unpaired *t* test where appropriate. Correction for potential confounders with a *p* ≤ 0.15 will be performed using multiple regression analysis. Considering the expected incidence of DB, the statistical power will allow to correct for two confounding factors. We expect at least anticoagulant medication to be a potential confounder for DB.

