## Background

### Delayed bleeding after endoscopic mucosal resection

In 2014, a national colorectal cancer screening (NCCS) program was introduced in the Netherlands [1]. The program is based on immunological fecal occult blood testing (iFOBT), followed by colonoscopy after a positive iFOBT result. During colonoscopy, the detection of colorectal cancer and advanced adenomas has been found to be 8% and 43%, respectively [2]. The treatment of advanced adenomas has resulted in a considerable spin-off of the NCCS program.

Endoscopic mucosal resection (EMR) is a safe and cost-effective method for resecting larger flat or sessile adenomas in the colorectum with no signs of submucosal invasion. However, delayed bleeding (DB) is the most prevalent complication and is reported in up to 12% after EMR. Identified risk factors of DB after EMR are anticoagulant drug use within 7 days of the procedure (OR 6.3; *P* = 0.005), polyp size and location in the colon with a 12% incidence rate of delayed bleeding in the cecum, 10% in the proximal ascending colon, 7% at the hepatic flexure, and 2–3% in the left colon [3–9].

Several preventive measures have been undertaken to reduce post-EMR bleeding, such as coagulation of visible vessels, prophylactic clipping (PC), or suturing of the EMR resection defect. Prophylactic coagulation of visible vessels in the resection defect has not been shown to decrease the incidence of DB [7]. However, PC has been reported in several studies to reduce DB especially in right sided EMR’s for lesions sized over 2 cm [10, 11]. Theoretically, a clip applies pressure to the underlying vessels in the EMR defect and results in increased mucosal healing [12], which may result in a reduced DB risk. Nonetheless, studies reporting on PC in EMR have several limitations, such as a retrospective design, inclusion of all sizes and types of polyps (pedunculated/flat, right/left-sided), lack of statistical power, and all reported studies were performed in tertiary referral centers, thereby not representing normal daily practice. Additionally, PC will lead to increased costs of EMR and it is unknown whether the additional costs of PC in high-risk patients (right sided flat polyps ≥ 2 cm) will outweigh the benefits of PC in terms of quality of life gains and/or cost savings related to prevention of DB [12].

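### Covariate adjustment of the delayed-bleeding comparison depends on observed imbalance and an undefined p ≤ 0.15 screen, instead of being fixed in advance for anticoagulant use

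*Protocol article*

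**What the plan says.** The Primary analysis section of the Protocol article first sets out an intention-to-treat comparison of delayed bleeding by a mixed regression model that allows for clustering and gives a relative risk. A second paragraph adds a conditional step: "In case of disbalances in baseline characteristics, potential confounders for DB will be determined with a" chi-square test or unpaired t test, with those at p ≤ 0.15 corrected for in a multiple regression.

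On how many covariates, it states: "Considering the expected incidence of DB, the statistical power will allow to correct for two confounding factors". On which, it says only: "We expect at least anticoagulant medication to be a potential confounder for DB". The Background has already identified that variable: "Identified risk factors of DB after EMR are anticoagulant drug use within 7 days of the procedure", with an odds ratio of 6.3.

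The section on randomization and treatment allocation describes 1:1 web-based allocation stratified by centre alone.

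The article leaves three things open:
- which association the p-value tests (with arm or with delayed bleeding);
- what happens if more than two variables pass;
- whether the adjusted estimate replaces the mixed-model relative risk or sits beside it.

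**The concern.** Allocation is randomised, so any baseline imbalance between arms is due to chance. A significance test of that imbalance asks a question whose answer is already known, and it says nothing about whether the variable predicts bleeding. If the screen is against arm, a strong known predictor enters the model only when chance happens to unbalance it. If the screen is against bleeding, the covariate set is chosen from the outcome data.

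Under either reading, the final form of the primary comparison is settled after the data are seen. With no stated hierarchy, two defensible results can exist and someone must choose between them. That choice, and the reproducibility of the primary analysis, is what is at stake.

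**Working it through.** **Inputs from the article.** Rates: "reduce delayed bleedings by 7.8% (from 9.8 to 2%) in a superiority design". Level: "With a 2-sided significance level of 5% (0.1% used as symmetric stopping boundaries during the interim-analysis, and 4.9% used as nominal significance level"). Size: "and power of 80%, a total of 310 patients are required". Inflation: "With an estimated drop out of 15%, a total of 356 patients". Odds ratio 6.3 for anticoagulant use (Background). Selection threshold p ≤ 0.15.

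**Assumed inputs.** Anticoagulant prevalence 20–35%; no centre effect in the simulations.

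**1. The plan's own sample size.** The exact power of Fisher's test at 155 per arm, 9.8% against 2%, two-sided 4.9%, is 80.2%, so 310 reproduces. 310 × 1.15 = 356.5, which gives 356.

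**2. Expected events.**
- At 310 patients: 155 × 0.098 + 155 × 0.02 = 15.2 + 3.1 = 18.3.
- At 356 patients: 178 × 0.098 + 178 × 0.02 = 17.4 + 3.6 = 21.0.

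**3. Screen against arm.** Only centre is stratified, so anticoagulant use passes p ≤ 0.15 in about 15% of trials by construction; simulation gives 14–15%. With k independent candidates, the chance that at least one passes is 1 − 0.85^k: 73% for k = 8 and 80% for k = 10 (both k assumed). These figures apply to this reading only.

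**4. Screen against delayed bleeding.** Simulation (4,000 trials per setting, 155 per arm) flags anticoagulant use in about 97–100% of trials. A hand check at 30% prevalence agrees:
- An overall risk of 5.9% and an odds ratio of 6.3 imply risks of about 2.5% in 217 non-users and 13.9% in 93 users, a difference of 11.4 points.
- Pooled standard error: √[0.059 × 0.941 × (1/93 + 1/217)] = 0.0292. The p ≤ 0.15 cut-off (z = 1.44) is therefore 4.2 points.
- Unpooled standard error: √[0.139 × 0.861/93 + 0.025 × 0.975/217] = 0.0374. Then (11.4 − 4.2)/3.74 = 1.92, a pass probability of about 97%.

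The article also makes the screen conditional on imbalance without defining imbalance, so the share of trials actually adjusted under this reading cannot be computed.

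**5. The screen against the limit of two.** With eight assumed binary candidates (prevalence 30%, three prognostic with log-odds 0.6), a screen against bleeding passes more than two variables in 34% of simulated trials with 5.9% bleeding in both arms. The article gives no order of entry.

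**6. Type I error (likelihood-ratio logistic tests).**

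| Result used | Anticoagulant model, tested at 0.049 | Eight candidates, 5.9% in both arms, tested at 0.05 |
|---|---|---|
| Unadjusted | 5.0–6.0% | 6.0% |
| Rule, screen against arm | 4.7–5.4% | 5.6% |
| Rule, screen against bleeding | 5.0–5.7% | 5.8% |
| Most favourable result | 6.2–7.1% | 6.9% |

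The first column rests on 4,000 trials per setting and the second on 3,000. At a rate of 6% the Monte Carlo standard error is √(0.06 × 0.94/4,000) = 0.4 points, so small differences among the first three rows are noise.

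**7. At the planned effect.** Adjusted and unadjusted verdicts disagree in about 2–4% of trials, and in about 7% at 9.8% against 4%. In one set of runs, always adjusting for anticoagulant use gave 88.2–88.3% power against 87.5–88.2% unadjusted. These exceed 80% because the likelihood-ratio test is less conservative than Fisher's.

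**The case against.** The strongest reply is that little goes wrong if the rule is followed as written. Step 6 bears this out: under either screen, type I error stays near that of the unadjusted test. A reader might infer that the rule itself inflates the error rate. The figures do not support that. The 6–7% requires picking the more favourable of two results, which the article does not provide for, and part of the excess over 4.9% is the small-sample behaviour of the test.

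A reader might also infer that the adjusted result is the primary one. The text does not say so. It opens with the mixed-model relative risk and never states that the correction replaces it. An analysis plan that is not shown may settle the order. But the protocol is not silent here: it states a rule, and that rule needs correcting wherever the order is settled.

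A third tempting inference is that two confounders overload the model. This rests on a convention of ten events per parameter, which is not in the article. Two confounders alone have 18.3/2 = 9.1 events each at 310 patients and 21.0/2 = 10.5 at 356. Counting treatment, the figures are 18.3/3 = 6.1 and 21.0/3 = 7.0. Even treatment plus one covariate misses that convention at 310 (9.1), so it cannot justify cutting two to one. With two fixed covariates the simulated type I error was 5.8%, against 6.0% unadjusted.

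Finally, the benefit of fixed adjustment is modest, as step 7 shows. That also stands.

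**Conclusion.** The point holds as one about specification. The imbalance trigger and the p ≤ 0.15 screen are a poor way to choose covariates in a randomised trial, and the sentence can be read in two ways that treat the one named predictor very differently: flagged in about 15% of trials under one and about 97–100% under the other. With no declared primary estimate, this leaves room to choose between results, worth roughly one percentage point of type I error (about 6–7% where the unadjusted test gives about 5–6%).

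The documents do not support saying that the rule, applied mechanically, is invalid, or that two covariates are too many. What is fair to say about the number two is that no event basis is shown for it.

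The simulated figures rest on the assumed prevalence of 20–35%, the published odds ratio of 6.3 and the omission of centre effects. The objection to testing chance imbalance needs none of these. The change should be made, but it does not threaten the trial's conclusions by itself.

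**What to change.** - Delete the imbalance trigger, the baseline tests used for selection and the p ≤ 0.15 threshold.
- Specify now that the primary mixed model contains treatment, centre and anticoagulant use (yes/no), whatever the baseline table shows.
- Declare the relative risk from that model the single primary estimate, with the unadjusted result as a sensitivity analysis.
- If a second covariate is wanted, name it in advance, state the event basis (about 18 events at 310 patients, 21 at 356) and plan a small-sample method such as penalised likelihood.

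The cost is wording only, with no added patients. The article already expects anticoagulant use to matter, so the variable is needed in any case. Because recruitment is under way, the change should be dated before the final analysis is unblinded. The downside is that covariates can no longer be added after the baseline table is seen, and the gain in power is small, about one point or less.

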#### Analyses of secondary outcomes

The secondary endpoints will be compared between study groups using Student’ *T* test or *χ*^2^ test whenever appropriate. Lastly, a cost-effectiveness analysis will be performed. As a societal perspective allows for a more complete economic evaluation as compared to a health care perspective alone, three cost categories will be analyzed: direct medical costs, direct non-medical costs, and indirect costs (see Supplementary File 1 for a definition of these secondary endpoints).

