## Methods

### Trial design

The CLIPPER trial is a nationwide multicenter randomized, parallel-group, patient-blinded superiority trial, comparing prophylactic clipping after EMR to standard care in 356 patients undergoing EMR for a non-pedunculated polyp in the proximal colon sized 20–60 mm in 19 hospitals of the Dutch EMR Study Group in the Netherlands. The trial will be conducted over a time period of 3 years. The study protocol was written in accordance with the SPIRIT guidelines [16, 17].

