### Study end points

The primary outcome is the incidence of clinically significant DB, defined as anal blood loss occurring after the completion of the procedure necessitating emergency department consultation, blood transfusion, prolongation of hospital stay, re-hospitalization, or re-intervention (either repeat endoscopy, angiography or surgery) [5, 10, 20–23]. Self-limiting bleeding managed on an outpatient basis is not considered to be DB.

PC may improve patients’ health status, prevent serious complications of DB, reduce the demand for healthcare, and lower costs. The secondary outcomes therefore are (1) severity of DB (see Supplementary File 1 for definition of DB severity), (2) procedure time, (3) perforation rate, (4) EMR scar evaluation at the first surveillance colonoscopy after 6 months, (5) adenoma recurrence rate at 6 months, (6) health-related quality of life, and (7) direct and indirect costs related to PC.

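### The non-economic secondary endpoints are compared without the centre factor used to randomise: the tests are valid, but conservative to the extent that centres differ

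*Protocol article*

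**What the plan says.** All references are to the protocol article.

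- **Randomization and treatment allocation:** "Participants are stratified by center with random block sizes of 2, 4, and 6 per stratum". Allocation is 1:1. Trial design places the study "in 19 hospitals of the Dutch EMR Study Group in the Netherlands".
- **Primary analysis:** delayed bleeding (DB) is analysed "using a mixed model regression analysis to correct for clustering of data". The cluster is not named. Patients with more than one lesion are excluded and each patient contributes one bleeding presentation, so centre (or operator within centre) is the evident candidate. The same section lists general tests ("test, Wilcoxon rank sum test", chi-square, Fisher). None of them uses centre.
- **Analyses of secondary outcomes:** "The secondary endpoints will be compared between study groups using Student" t-tests or chi-square tests, whichever fits. No centre term appears.
- **Study end points:** "The secondary outcomes therefore are (1) severity of DB", followed by procedure time, perforation, scar evaluation, adenoma recurrence at 6 months, quality of life and costs.
- **Economic evaluation:** costs and QALYs have their own plan, with bootstrapping and, if baseline correction is needed, regression on net monetary benefit.

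**The concern.** The trial builds centre into its randomisation and models clustering for its primary endpoint, then states secondary tests that use neither. This is a stated method and not a detail left open.

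Blocking within centre makes the arms nearly equal in their mix of hospitals, so centre differences largely cancel from the treatment difference. A two-sample test does not know this. It counts centre differences as noise, reports too large a standard error, and rejects less often than its nominal level.

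Centre differences are plausible from the article itself. Under Surveillance, scars are read by the endoscopist and suspect lesions are treated by local protocol. Under Standard care, soft coagulation of the margins, used against recurrence, is discretionary. At stake is the reported precision for procedure time, scar findings and recurrence. The validity of the comparison is not at stake.

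**Working it through.** **Plan's own figure.** The article states no precision, ICC or between-centre variance for any secondary endpoint, so there is nothing to reproduce on this point. Its sample size enters only as N: "a total of 356 patients (2 × 178) are required to demonstrate this effect", which follows from 310 × 1.15 = 356.5.

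**Inputs from the article.** 19 centres; blocks of 2, 4 and 6; 1:1; N = 356 for procedure time; 356 × 0.85 = 302.6, taken as 302, for the 6-month endpoints; a clip-artifact rate of 30% (Scar surveillance).

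**Assumptions.** ICC 0 to 0.30 for procedure time and 0 to 0.10 for the binary endpoints; a recurrence rate of 15%.

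**Formula.** With total variance 1 and between-centre share ICC, the unadjusted analysis uses a variance of about 1 and the within-centre analysis uses 1 − ICC. The half-width ratio (adjusted/unadjusted) is therefore about √(1 − ICC): 0.975, 0.949, 0.894 and 0.837 at ICC 0.05, 0.10, 0.20 and 0.30. With only 19 centres the sample captures about 18/19 of the between-centre variance, so the ratio is slightly nearer 1. At ICC 0.30: √[0.70 / (0.70 + 0.30 × 18/19)] = √(0.70/0.984) = 0.843.

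**Simulation, procedure time** (1,500 runs per row, equal centres, N = 356, SD 1):

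| ICC | Half-width unadjusted | Half-width centre-adjusted | Ratio | Excess width (1/ratio − 1) | Type I error, unadjusted / adjusted |
|---|---|---|---|---|---|
| 0.05 | 0.2082 | 0.2035 | 0.977 | 2% | 3.7% / 4.1% |
| 0.10 | 0.2079 | 0.1981 | 0.953 | 5% | 4.2% / 5.1% |
| 0.20 | 0.2076 | 0.1869 | 0.900 | 11% | 3.0% / 4.8% |
| 0.30 | 0.2068 | 0.1746 | 0.844 | 18% | 2.5% / 5.3% |

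At ICC 0 and 0.01 the ratio is 1.00. The Monte Carlo standard error of a 5% rejection rate is √(0.05 × 0.95/1500) = 0.6 percentage points, so only the last two rows show clear conservatism. Unequal centre sizes give ratios of 0.979, 0.956, 0.904 and 0.851.

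**What is lost.** At ICC 0.30 the actual spread of the estimate is the same either way (0.089 unadjusted, 0.088 adjusted). The unadjusted analysis reports a standard error of about 0.2068/1.967 = 0.105. The estimate already has the benefit of blocking; the unadjusted standard error does not show it.

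**Simulation, binary endpoints** (risk difference, N = 302, equal centres):

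| Rate | ICC | Half-width, unadjusted → adjusted (percentage points) | Ratio | Excess width |
|---|---|---|---|---|
| 15% | 0.05 | 8.03 → 7.84 | 0.977 | 2% |
| 15% | 0.10 | 8.03 → 7.64 | 0.952 | 5% |
| 30% | 0.05 | 10.38 → 10.14 | 0.977 | 2% |
| 30% | 0.10 | 10.35 → 9.86 | 0.953 | 5% |

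At ICC 0 the ratio is 1.002 at both rates, so adjusting costs almost nothing if centres do not differ.

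**Sparse endpoints.** At 155 per arm (310/2), the planning rates of 9.8% and 2% give 15.2 and 3.1 patients with DB. That is about 18 over 19 hospitals, or roughly one per stratum. Centre-stratified analysis of DB severity would have almost nothing to work with. No perforation rate is given; perforation is assumed to be at least as sparse.

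**The case against.** The strongest reply is that nothing here is invalid. Unadjusted tests after centre-stratified randomisation keep their level and err on the cautious side. The article condenses a fuller plan, and the tests are to be used as appropriate. That stands as to severity. It does not remove the point, because the article states a method that is out of line with its own design and primary model.

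Several stronger readings are tempting, and the documents do not support them:

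- **The tests waste the equivalent of 30 to 90 patients.** This comes from about 303 × 0.10 = 30 to 303 × 0.30 = 91, which takes a 10–30% centre share for every endpoint. No such share is documented, and the range leaves out the low ICCs where the loss is nil to 2%.
- **The whole operator effect would be recovered.** Blocking is by centre. Variation between endoscopists within a hospital is not balanced by it and is not removed by a centre term.
- **Every secondary endpoint is affected.** The economic outcomes have a separate plan.
- **DB severity will be compared among bleeders only.** The article does not say so, and the severity definition is in a supplement not shown here.
- **The plan prescribes intervals that are too wide.** The secondary section names tests and no intervals. The widths above describe what those tests imply.

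**Conclusion.** The point holds as a minor matter of efficiency and consistency for procedure time, scar findings and recurrence. The planned tests are valid, and conservative to the extent that centres differ. The size depends wholly on an ICC that the documents do not give. For procedure time the cost is negligible at low ICC and becomes noticeable only from about 0.20. For recurrence and scar findings it is small over the range examined, and the 15% recurrence rate used there is also assumed. The results apply to mean differences and risk differences. A centre-adjusted odds ratio would not necessarily have a narrower interval. No conclusion about bias or inflated false positives follows.

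**What to change.** Before the final analysis, amend Analyses of secondary outcomes so that centre is carried in, as clustering is for the primary endpoint:

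- **Procedure time:** linear mixed model with treatment as a fixed effect and centre as a random effect, on the log scale if skewed.
- **Adenoma recurrence and scar findings:** centre-stratified Mantel-Haenszel risk difference with 95% confidence interval, or the same mixed model as for DB.
- **Perforation and DB severity:** no centre stratification, with the reason (too few events) stated.
- **Costs and QALYs:** leave under the existing economic plan.

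Centre is known for every patient from randomisation, so no new data are needed. The cost is a few lines of wording and a little programming.
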